### **3. OBJECTIVES**

#### **3.1 General objectives**

- 3.1.1 Establish a long-term program of systematic evaluation and follow-up of cardiorespiratory health and performance of high elite athletes.
- 3.1.2 Evaluate the prevalence of respiratory, circulatory and metabolic problems among high-level athletes.
- 3.1.3 Evaluate the effects of treatments on cardiorespiratory conditions and exercise performance in athletes who need asthma medication.

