#### **3.2 Specific objectives**

- 3.2.1 Determine seasonal and long-term changes in airway caliber, airway responsiveness to methacholine and inflammation in high-level athletes involved in long-term intense training.
- 3.2.2 Evaluate the perception of respiratory symptoms after various airway challenges and evaluate if there is discordance between subjective and objective assessment.
- 3.2.3 Assess the efficacy of asthma medications in asthmatic athletes.

3.2.4 Assess R-R variability in high-level athletes overtime.

3.2.5 Assess cardiac activity in high-level athletes.

3.2.6 Evaluate maximal aerobic capacity in high-level athletes.

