**3.2.7. Evaluate the effect of deep inspiration avoidance and airway response to methacholine in athletes.**

## **4. HYPOTHESES**

4.1 Cardiorespiratory problems are frequent and often unrecognized in high-level athletes.

4.2 A systematic evaluation of cardiorespiratory function in athletes may improve their condition and sports performance in recognising undiagnosed cardiorespiratory problems who would benefit from.

4.3 Long-term intense training is associated with an increase in airway responsiveness, asthma, and structural change of heart (hypertrophy).

4.4 Response to asthma therapy is poor in asthmatic athletes, compared to non-athletes, suggesting different underlying pathophysiologic mechanisms.

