## **5.2 Subjects selection**

High-level athletes who are members of one of the 11 National Teams in the Quebec area. This includes athletes with the mention of *excellence, elite, relève or espoir*.

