**Eucapnic Voluntary Hyperventilation Test:** The method described by Argyros et al. will be used. Briefly, eucapnic hyperventilation consist in hyperventilating dry air containing 5% of CO2 at room temperature, during 6 min at 30 X baseline FEV1, i.e. 85% of maximal voluntary ventilation. FEV1 will be recorded before and 1, 3, 5, 10, 15 and 20 minutes after the test to see if bronchospasm appear. At 10% fall in FEV1 the tests is considered positive. Before each FEV1 manoeuver, the Borg score for perception of respiratory symptoms will be noted.

**Spirometric field testing:** FEV1 and FVC will be measured before and 1,5,10,15 and 20 minutes after maximal exercise to see if bronchospasm appear. At 10% fall in FEV1 the tests is considered positive. Before each FEV1 manoeuver, the Borg score for perception of respiratory symptoms will be noted. Exercise will be specific for each sport. Maximal exercise will be defined with maximal heart rate for each subject. The duration of exercise will be approximately 10 to 12 minutes.

**Induced sputum analysis:** Sputum will be obtained with hypertonic saline by the method described by Pin et al. and modified by Pizzichini et al. which involves inhaling increasing concentrations of saline (3, 4, and 5%) for seven minutes each through a mouthpiece without a valve or nose clip. Sputum processing will be performed as previously reported. Cytospins will be prepared. One cytospin will be dried and Wright-stained, and a 400 non-squamous cell differential will be performed. IS supernanant will be frozen in aliquots for delayed measurements of mediators and cytokines: VEGF, alpha-2 macroglobulin, ECP and MPO. Mucosal injury will be assessed by looking at the number of desquamated epithelial cells in the samples.

**Assessment of efficacy of asthma medication:** In the athletes who require a medication to treat asthma, we want to evaluate if the bronchodilators and inhaled corticosteroids are effective, as

they are in normal asthmatic (non-athletes). We will collect preliminary data, by analyzing the evolution of the respiratory symptoms following the medication administration. Afterwards, we will see if it is pertinent to make a controlled randomized studies.

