## **4.5 Sample size**

As such study has never been done, we will recruited 100 subjects. There was no control group. Controls subjects will be include in under-studies.

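### Hypothesis 4.4 compares athletes with non-athletes whom the protocol does not enrol, and medication is judged on symptoms alone although objective 3.1.3 promises more

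*Protocol*

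**What the plan says.** Five parts of the protocol bear on this point.

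- **Hypothesis 4.4** (section 4, Hypotheses): "Response to asthma therapy is poor in asthmatic athletes, compared to non-athletes, suggesting different underlying pathophysiologic mechanisms".
- **Objectives.** General objective 3.1.3: "Evaluate the effects of treatments on cardiorespiratory conditions and exercise performance in athletes who need asthma medication". Specific objective 3.2.3: "Assess the efficacy of asthma medications in asthmatic athletes".
- **Population** (section 5.2): "High-level athletes who are members of one of the 11 National Teams in the Quebec area". Section 5.2.1 adds a minimum of 10 training hours per week for athletes.
- **Controls** (section 4.5, Sample size): "There was no control group. Controls subjects will be include in under-studies".
- **Method for medication** (section 4.4.1, paragraph on efficacy of asthma medication). The question is whether bronchodilators and inhaled corticosteroids work in athletes as they do in non-athlete asthmatics. The method is: "We will collect preliminary data, by analyzing the evolution of the respiratory symptoms following the medication administration". Whether a randomised controlled study is worthwhile is to be decided afterwards.

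Section 1 (Background) also remarks that athletes often do not perceive the symptoms of these conditions well.

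**The concern.** Hypothesis 4.4 is comparative. It needs the response to therapy in two groups, asthmatic athletes and asthmatic non-athletes, and it then infers a difference in mechanism. The protocol describes data collection in the first group only. If 4.4 stays as worded, a poor response seen in athletes may be reported as poorer than in non-athletes, and as evidence of a different disease process, with nothing in the study to support either step.

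The second problem concerns the outcome. Where symptoms are poorly perceived, a flat symptom course after medication can mean that the drug did little or that the athlete does not perceive the change. Symptoms alone cannot separate the two. They also do not cover exercise performance, which objective 3.1.3 names explicitly.

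**Working it through.** **1. What 4.4 needs and what is planned.** The quantity is

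D = mean response in treated asthmatic athletes − mean response in treated asthmatic non-athletes.

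| Term | Source in the protocol | Planned |
|---|---|---|
| Athletes | Sections 4.5 and 5.2 | The asthmatic, treated part of 100 athletes |
| Non-athletes, main cohort | Section 4.5: "There was no control group" | 0 |
| Non-athletes, sub-studies | Section 4.5, next sentence | Number, population, treatment and outcome not given |
| Visits 7 to 9 (section 5.1) | Volunteer athletes, deep inspiration avoidance | No non-athletes, no asthma therapy |

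The second term of D has no data, so D cannot be estimated. The inference about mechanisms depends on D and goes with it.

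**2. The plan's own figure.** Section 4.5 sets 100 subjects without an effect size, standard deviation, rate or power, so the number can be neither reproduced nor refuted.

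**3. What a comparison group would have to look like (illustration only).** Inputs from the protocol are 100 subjects, asthma prevalence in athletes of 9 to 55% (section 2.1), and the figures of 20.7% and 22.4% from cited Olympic cohorts (sections 2.1.2 and 2.1.3). Assumptions are an equal-sized group of treated non-athlete asthmatics, SD = 1, normal approximation, two-sided alpha 0.05 (the protocol gives a 95% level without sidedness) and 80% power.

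- Detectable difference = (1.960 + 0.842) × √(2/n).
- Power for 0.5 SD = Φ(0.5/√(2/n) − 1.960).

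| Prevalence | Asthmatic athletes, n | Detectable difference | Power for 0.5 SD |
|---|---|---|---|
| 9% | 9 | 1.32 SD | 18% |
| 20.7% | 21 | 0.86 SD | 37% |
| 22.4% | 22 | 0.84 SD | 38% |
| 55% | 55 | 0.53 SD | 75% |

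Conversely, n per group = 2 × (1.960 + 0.842)²/d², which gives 63 for d = 0.5 and 25 for d = 0.8. These counts are of asthmatic athletes. Those who start treatment during follow-up may be fewer.

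**4. Promised effects against the measured outcome.**

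| Measure | Scheduled at visits (section 5.1) | Linked to medication in 4.4.1? |
|---|---|---|
| Respiratory symptoms | 1 and 4 (questionnaire) | Yes |
| FEV1 and its fall after hyperventilation | 1 and 4 | No |
| PC20 methacholine | 1 and 4 | No |
| Sputum eosinophils | 1 and 4 | No |
| VO2max | 2 and 5 | No |

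The measures that would answer objective 3.1.3 are already repeated, but the medication assessment does not use them.

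**5. Whether these tests can serve as before-after data.** Section 5.1 plans one round of testing in the competing season and one in the resting period each year, for at least 3 years. I read visits 1 to 3 and 4 to 6 as those two rounds. A change from visit 1 to visit 4 then mixes treatment with training phase. A cleaner pair uses the same phase in different years. If later years repeat the schedule, 3 years give 3 tests per phase, and a pair exists only where treatment starts between two of them. The protocol does not time tests to the start of treatment.

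**The case against.** The best reply is that this component is modest by design. Section 4.4.1 calls the data preliminary and defers a randomised study. Section 4.5 promises controls in sub-studies. A hypothesis is a conjecture, here motivated by the remark in section 2.1.2 that asthmatic athletes often seem refractory to treatment. No comparative analysis is prespecified. Much of this stands, and it limits the point to a correctable mismatch. It does not rescue 4.4, which is listed as a study hypothesis without any limit, while the promised controls are too unspecified to test it.

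A reader might go further in four ways that the documents do not support.

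- **That objective 3.2.3 also compares with non-athletes.** It refers to asthmatic athletes only. The comparison is in hypothesis 4.4 and in the benchmark of section 4.4.1. Nor does 4.4 claim efficacy; it predicts a poor response.
- **That no controls will ever exist.** The accurate criticism is that the promised controls are unspecified.
- **That regression to the mean measures the bias in 4.4.** The protocol gives neither the symptom level at treatment start nor a test-retest correlation, and some athletes may already be on medication at visit 1. Regression to the mean would also look like improvement, which works against a hypothesis of poor response. It bears only on reading 3.2.3 as efficacy.
- **That the protocol declares symptoms unreliable.** Objective 3.2.2, on perception after airway challenges, asks the study to "evaluate if there is discordance between subjective and objective assessment", which is an open question. The firmer conflict is with objective 3.1.3 and the Background remark. Symptoms are the only outcome of the medication assessment, not of the protocol as a whole.

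**Conclusion.** The point holds in two limited parts.

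First, the comparison in hypothesis 4.4 cannot be tested, nor can the inference about mechanisms. The number of treated non-athletes specified is zero. This follows from reading the sections together and needs no assumption, except that no sub-study supplying such controls is specified outside this document. The detectable differences above show only what an equal-sized comparison group could achieve, under an assumed SD of 1 and background prevalences.

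Second, the medication method is narrower than objective 3.1.3. It names symptoms only, although objective respiratory and performance measures are already scheduled.

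Both should be corrected, because they decide what the study may conclude about asthma therapy in athletes. Neither affects the prevalence objectives.

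**What to change.** 1. **Hypothesis 4.4.** Restate it as an exploratory, uncontrolled description of response within asthmatic athletes, with no comparative or mechanistic conclusion. If the comparison is to stay, name the sub-study that supplies treated non-athlete asthmatics, with its number, population, treatment and outcome.
2. **Objective 3.2.3.** Label it preliminary and uncontrolled, in line with section 4.4.1.
3. **Section 4.4.1, medication paragraph.** Add FEV1, fall after hyperventilation, PC20, sputum eosinophils and VO2max alongside symptoms, so that the method matches objective 3.1.3.
4. **Timing.** Record medication status at every visit. The medical questionnaire, which asks about medication, is scheduled only at visits 1 and 4 of the first six. Where an athlete has tests before and after starting treatment, compare within the same training phase across years.

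Items 1 to 3 need rewording and no new tests, unless the comparison is kept, which means recruiting a second group. Item 4 adds a short record per visit. The stated claim becomes weaker, and fewer athletes will have usable same-phase pairs, because tests are not timed to treatment. Objective measures do not make the comparison controlled: they too can regress to the mean, so the result remains descriptive.

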**4.5. Deep inspiration avoidance before methacholine inhalation enhances the fall of FEV1 in athletes.**

## **5. METHODS**

### **5.1 Study design**

Visits will be done by athletes to the laboratory on 2 occasions each year over a period of at least 3 years and field-tests at 2 times per year according to the annual planning schedule of each team, including 1 testing during competing season and 1 in the resting period. (For example, speed skaters begin their season in September and their resting period is in the month of April.) On the

first visit, consent form will be explained by the investigator or his/her delegate and signed by the subject. At the first visit, physical examination, medical questionnaire regarding their health condition, their family history of disease, their medication and their history in practicing their sport will be performed. Also, respiratory questionnaire, blood sample, eucapnic hyperventilation test, allergy prick skin test, methacholine challenge with Borg score and sputum analysis will be done, as well as the Holter. At the second visit maximal aerobic capacity test and MAPA will be done. At the third visit, spirometric field testing will be performed for each sports. Visit 4, 5 and 6 will be the same as visit 1, 2 and 3, except for allergy test which will be done only on the first visit.

| Visits                                 | 1 | 2 | 3 | 4 | 5 | 6 | 7 | 8 | 9 |
|----------------------------------------|---|---|---|---|---|---|---|---|---|
|                                        |   |   |   |   |   |   | X |   |   |
| Reading and signature of the assent    | X |   |   |   |   |   |   |   |   |
| Physical exam                          | X |   |   | X |   |   |   |   |   |
| Medical questionnaire                  | X |   |   | X |   |   |   |   |   |
| Anthropometric parameters              |   | X |   |   | X |   |   |   |   |
| VO2max test with ECG                   |   | X |   |   | X |   |   |   |   |
| Blood sample                           | X |   |   | X |   |   |   |   |   |
| Respiratory questionnaire              | X |   |   | X |   |   |   |   |   |
| Eucapnic hyperventilation test         | X |   |   | X |   |   |   |   |   |
| Allergy tests                          | X |   |   |   |   |   |   |   |   |
| Methacholine test + Borg score         | X |   |   | X |   |   | X | X | X |
| Induced sputum                         | X |   |   | X |   |   |   |   |   |
| Spirometric field testing              |   |   | X |   |   | X |   |   |   |
| Holter (heart rate variability)        | X |   |   | X |   |   |   |   |   |
| MAPA (24hre blood pressure monitoring) |   | X |   |   | X |   |   |   |   |

**In an addition, volunteer athletes will have three supplementary visits during the summer season, inside 10 days (visit 7, 8 and 9). These three visits will include different methacholine challenge protocols. The first methacholine challenge (visit 7) will be the same than in the first visit of the excellence protocol (see Table above, standard Juniper protocol), but no**

eucapnic voluntary hyperventilation challenge will be performed before. During the visit 8, a single-dose methacholine will be performed without previous deep inspiration during 20 minutes before the first inhalation. During the visit 9, a single-dose methacholine will be performed without deep inspiration avoidance. These protocols were previously used in asthmatic, control and obese subjects (Simard et al. 2005, Boulet et al. 2005).

## **5.2 Subjects selection**

High-level athletes who are members of one of the 11 National Teams in the Quebec area. This includes athletes with the mention of *excellence, elite, relève or espoir*.

### **5.2.1 Inclusion criteria**

#### All subjects

1. All subjects will provide a written informed consent and the study will be approved by the institutional ethics committee.
2. Subjects will be aged from 18 to 45 years.
3. Athletes will be training for at least 10 hours per week.

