### **4.4.1. Pulmonary evaluation**

**Questionnaires and asthma control assessment:** Apart from current subjects' characteristics (age, sex, duration of asthma, etc.), current respiratory symptoms will also be reported according to The European Community Respiratory Health Survey (ECRHS). Outdoor and indoor training duration will be also noted.

**Physical Examination:** A cardio-thoracic examination including blood pressure will be performed at the baseline visit.

**Allergy skin prick tests:** Atopy will be determined using skin prick tests to a battery of common aeroallergens. Normal saline and histamine will be used as negative and positive controls respectively. Skin wheal diameter will be recorded at 10 min as the mean of 2 perpendicular measurements. A positive response will be defined as a skin wheal diameter of 3 mm or more.

**Spirometry:** FEV1, FVC and FEF25-75% will be measured from flow-volume curves performed according to the American Thoracic Society (ATS) specifications. Predicted values will be obtained from European Respiratory Society (ERS). The baseline FEV1 will be calculated as the best of three reproducible values (with maximum change of 5%). Spirometry will be performed with an ATS approved spirometer.

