## **4.6 Analysis**

Descriptive statistics will be used to summarize the subjects' clinical characteristics. Normally distributed data will be reported as the arithmetic mean and standard deviation. Non-normally distributed data such as sputum cell count will be reported as the median and interquartile range. Non normally distributed data will undergo the most appropriate transformation to be normalised. A Wilcoxon signed rank test will be used to compare the data that could not be normalised. Significance will be accepted at a level of 95%. The analysis will be performed using the SPSS 10.0 statistical package (Chicago IL).

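### Hypothesis 4.3 concerns the effect of long-term training, but the study has no unexposed comparison and the one test named is paired, so within-athlete change cannot be attributed to training

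*Protocol*

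**What the plan says.** Section 4 (Hypotheses), item 4.3, reads: "Long-term intense training is associated with an increase in airway responsiveness, asthma, and structural change of heart (hypertrophy". This is a statement about an exposure and three outcomes.

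The population is set in section 5.2, "High-level athletes who are members of one of the 11 National Teams in the Quebec area", and in section 5.2.1, "Athletes will be training for at least 10 hours per week". Section 4.5 adds: "There was no control group. Controls subjects will be include in under-studies". It gives no number, definition or matching for those controls and does not connect them to hypothesis 4.3.

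Section 4.6 covers descriptive summaries and transformation, and names one test: "A Wilcoxon signed rank test will be used to compare the data that could not be normalised". No test is named for data that are normal or have been normalised.

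Exposure information is collected. Section 4.4.1 says: "Outdoor and indoor training duration will be also noted". Section 5.1 has a history of sport practice taken with the medical questionnaire at visit 1. Section 4.6 mentions neither. Section 5.1 also places one testing in the competing season and one in the resting period, over at least 3 years.

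**The concern.** An association between training and an outcome can be estimated only where training differs, either between people or within a person in a way not tied to something else. Here no subject is unexposed or lightly exposed. The one named test compares an athlete with himself or herself.

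Such a comparison serves objective 3.2.1, which asks for seasonal and long-term change. For hypothesis 4.3 it mixes long-term training with at least three other causes of change:

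- **Ageing** over a follow-up of at least 3 years.
- **Competing or resting phase**, which section 5.1 builds into the timing of the tests.
- **Treatment begun because visit 1 found a problem.** Hypothesis 4.2 expects the evaluation to recognise undiagnosed conditions and improve the athletes' state.

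The bias can go either way. Ageing or phase could produce a change that looks like a training effect, and treatment of newly found asthma could hide a real worsening in PC20. The study could therefore support or fail to support 4.3 for reasons unrelated to training.

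**Working it through.** **The plan's own figure.** Section 4.5 sets the size as follows: "As such study has never been done, we will recruited 100 subjects". It gives no effect size, variance, power or dropout, so 100 cannot be reproduced. The point does not depend on it.

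**Step 1: which statement each element can answer**

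| Element | Seasonal and long-term change (objective 3.2.1) | Association with long-term training (hypothesis 4.3) |
|---|---|---|
| Repeated visits, paired test (5.1, 4.6) | Yes | Not isolated from ageing, phase or treatment |
| Competing versus resting phase (5.1) | Yes, seasonal part | Short-term load only, and tied to season |
| Unexposed group (4.5) | Not needed | None in this study |
| Sport history, indoor and outdoor duration (5.1, 4.4.1) | Not needed | Could serve as an exposure gradient; not named in 4.6 |

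**Step 2: how easily non-training drift gives a significant paired test.** Assume training has no effect and the outcome drifts by *d* standard deviations of the within-athlete change. The significance level in section 4.6 is read as two-sided 5%. The approximate rejection probability is

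Φ(d√n − 1.96) + Φ(−d√n − 1.96).

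For n = 100 and d = 0.2, d√n = 2.0, which gives Φ(0.04) + Φ(−3.96) = 0.516. The other values follow in the same way. The last three columns come from 3,000 simulated studies per row with normal changes.

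| Assumed drift d | Paired, formula | Wilcoxon signed rank | Slope of change on weekly hours | Versus 100 controls with same drift |
|---|---|---|---|---|
| 0.1 | 17.0% | 15.4% | 4.7% | 5.8% |
| 0.2 | 51.6% | 49.2% | 5.1% | 5.1% |
| 0.3 | 85.1% | 82.4% | 4.6% | 5.2% |
| 0.5 | 99.9% | 99.8% | 4.6% | 4.8% |

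The drift sizes, the distribution of hours (10 plus a gamma variable with shape 2 and scale 4) and the control group are all assumptions. The slope stays near 5% because drift was taken as unrelated to hours. If drift depends on age or treatment, and those are related to training dose, adjustment is needed to keep it there.

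**Step 3: what an internal exposure-response analysis could detect.** With one value per athlete, two-sided 5% and 80% power,

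r = tanh((1.96 + 0.842)/√(n − 3)).

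- n = 100: tanh(2.802/√97) = 0.277
- n = 80: tanh(2.802/√77) = 0.309
- n = 60: tanh(2.802/√57) = 0.355

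The numbers 80 and 60 are assumed counts of analysable athletes.

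**Step 4: clustering.** With 100 athletes in 11 teams the mean team size is 100/11 = 9.1. If training dose varies mainly by team and the intraclass correlation is 0.05 to 0.10 (assumed), the design effect is 1 + 8.1 × 0.05 = 1.40 to 1 + 8.1 × 0.10 = 1.81. The effective n is about 71 to 55, and the detectable r becomes about 0.33 to 0.37. Methacholine is given only up to 128 mg/ml (section 4.4.1), so PC20 is censored in non-responders, which raises the figure further.

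**The case against.** **Model choice belongs in an SAP.** This is the strongest objection. No SAP is shown, section 4.6 is a short summary that excludes no analysis, and the exposure variables are collected. It stands as far as the absence of a regression goes: it cannot be said that training dose will go unused. It does not reach the design. An SAP can choose a model, but it cannot supply an unexposed group to a study that has none.

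**Controls are foreseen.** Section 4.5 does place controls in sub-studies, so an outside comparison is not ruled out. As written, however, those controls are undefined and unconnected to hypothesis 4.3.

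**Stronger readings that the protocol does not support**

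- A reader might infer that all testing is paired. Section 4.6 names the signed rank test only for data that could not be normalised and names nothing for the rest.
- A reader might infer that a within-athlete comparison is uninformative because exposure is constant in it. Section 5.1 contrasts competing and resting phases, and cumulative exposure grows over follow-up. The weakness is confounding, not absence of contrast.
- A reader might infer that the investigators will present change over time as a training effect. The protocol nowhere says so, and objective 3.2.1 is descriptive. The protocol simply sets no limit on that interpretation.

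**An internal exposure-response analysis has its own limits.** This stands. Years in the sport will probably track age, athletes with symptoms may have cut their training, and the background section presents sport and environment as determinants of airway disease.

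**Conclusion.** The point holds. Hypothesis 4.3 asserts an association with long-term training, while the population, the lack of a control group and the one named test support only within-athlete change. That change answers objective 3.2.1 and should not be taken as evidence for 4.3.

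The illustrated size is that a drift of 0.2 to 0.3 SD unrelated to training gives a significant paired result in about half to 85% of studies of 100 athletes. This depends on the assumed drift, for which the protocol gives no figure. The internal alternative is feasible for moderate associations: r of about 0.28 at n = 100, 0.31 at n = 80 and 0.355 at n = 60, all of them optimistic because clustering and censoring are ignored.

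The hypertrophy part of 4.3 is weaker still. Section 5.3.2 takes echography from clinical practice, and the visit table does not schedule it.

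This should be corrected, but it does not undermine the descriptive aims of the programme.

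**What to change.** 1. State in hypothesis 4.3 and section 4.6 that this study makes no unexposed comparison, and that within-athlete change is descriptive and not evidence of a training effect. Either define the sub-study controls in section 4.5 and link them to 4.3, or say that they do not bear on it.
2. Present within-athlete change also by whether asthma medication changed between visits 1 and 4. The medical questionnaire, scheduled at both visits, covers medication.
3. Examine the airway and asthma parts of 4.3 as an internal exposure-response association with sport history and indoor and outdoor training duration. Specify that these are recorded as years and weekly hours, which the protocol does not now do. State whether the outcome is level or change. Adjust for age, sex, atopy, sport or environment and testing phase, allow for clustering by team, and treat PC20 as censored at 128 mg/ml.
4. Label hypertrophy exploratory.

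The cost is wording in two or three sections and a fixed unit for two questionnaire items, with no new subjects, visits or tests. The downside is that adjusting for age may remove much of the contrast in years of sport, reduced training among symptomatic athletes may weaken the association, and the result would support association only, not causation.
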